#### Mediation analysis

Whilst well-powered to detect modest effect sizes of 0.29, the sample size also means that we should have power to assess the CMOCs with a selection of multi-level moderation, mediation and mediated moderation models. Nevertheless, more complex models and effects such as the mediated direct effect mean sensitivities of the tests will be lower and detectable effects will necessarily be larger. Estimates of power for mediation and moderation analyses will depend on the CMOCs selected for testing but here we give some guidelines. For mediation, taking a simplistic approach using Table 3 from Fritz and McKinnon 2007 [66], a sample size (assuming the loss to follow up rates above) of 46 schools of cluster size 12 or 11 and ICC of 0.07 gives effective sample sizes of 308 and 292 (or 412 and 386 for an ICC of 0.03) and will provide 80% power to detect small to moderate mediation effects with a and b path coefficients of > 0.26. The minimum sample size for this permutation of effects (minimum 148) allows a substantial buffer (50%) wherein the true sample size needed is larger due to the effects of clustering on the variance of the indirect effect being underestimated.

**Fig. 2 Fig2:**
[figure not shown]
Power curves for moderation analyses

#### Moderated mediation analysis for CMOCs

In a moderated mediation, there are four variables: the independent variable; the outcome; the mediator; and a fourth variable which moderates the indirect path (either path a, path b or both). For illustration purposes, we use the case of a model in which the moderation happens to the a pathway only and assume gender moderates the relationship between treatment condition and the hope outcome. We use the above result for moderation as an estimate of the power for the moderated a pathway. Similarly, we can use a further simulation to find power of the b path, a model consisting of two predictors representing paths from the mediator and independent variable to the outcome. Assuming that the effects are independent, the power of the mediation or joint model is the power of the a path * power of the b path. If the value of this product is 0.8 or greater, then the a * b pathway will have 80% power. For example, this might occur if the power of the a path was 0.81 and the power of the b path 0.99 corresponding to a and b paths of at DE = 1.79 (the more conservative ICC estimate assuming missingness of 8% and 1 cluster per group). Other scenarios are shown in Table 5 along with the power curves for the b path from which the coefficients corresponding to power levels can be read in Fig. 3. By Fritz and Mckinnon’s schema, we would expect the moderated a path effect size to be large and the b path to be medium, ranging small-medium to medium-large.

**Table 5 Tab5:** Power scenarios for moderated mediation

*N* Clusters	*N* individuals	Design effect	Missing	Power a	Power b	Overall power	a	b
46	552	1.79	8%	0.81	0.99	0.80	0.65	0.49
46	552	1.79	8%	0.85	0.94	0.80	0.68	0.40
46	552	1.79	8%	0.9	0.89	0.80	0.74	0.36
46	504	1.73	15%	0.81	0.99	0.80	0.66	0.50
46	504	1.73	15%	0.85	0.94	0.80	0.70	0.41
46	504	1.73	15%	0.9	0.89	0.80	0.75	0.34
46	552	1.34	8%	0.81	0.99	0.80	0.56	0.43
46	552	1.34	8%	0.85	0.94	0.80	0.59	0.35
46	552	1.34	8%	0.9	0.89	0.80	0.65	0.31
46	504	1.31	15%	0.81	0.99	0.80	0.58	0.44
46	504	1.31	15%	0.85	0.94	0.80	0.62	0.36
46	504	1.31	15%	0.9	0.89	0.80	0.67	0.33

**Fig. 3 Fig3:**
[figure not shown]
Power curves for the b path

### Data management and analysis

#### Data management

Pseudonymised survey data will be collected using tablets via an online platform and saved on secure servers. Information linking participant IDs to their personal information and any data that contains participant information (e.g., audio recordings, transcripts) will be kept on a secure server or a password-protected computer. Hard copies that contain participant information (e.g., consent forms) will kept in locked cabinets. Audio recordings of interview and focus group discussions will be transcribed in full by the research team and securely transferred to translators. The translations will be anonymised, stored on password protected devices and transferred securely to researchers involved in the analysis. All reporting will be anonymised. To facilitate any secondary analyses, we will retain anonymised data for 20 years after the study as per MRC guidance.

#### Qualitative analysis

To analyse qualitative data pertaining to mechanisms of change and contextual factors, we will use dimensional analysis. This is a variant of grounded theory useful for refining CMOCs because of its focus on identifying and organising dimensions of experience — meanings, processes, conditions and consequences [67]. For analyses of implementation data, we will use the thematic analysis. We will develop a coding framework with deductive codes informed by topic guides and also allow codes to emerge from the data (inductive coding). Where possible, the researcher who conducted the interviews/focus group discussions will be involved in the transcription and analysis, and we will conduct member checks to validate the findings.

#### Quantitative analysis

A detailed, pre-specified statistical analysis plan will be finalised and approved by the Data Monitoring Committee (DMC) and the independent statistician of the Trial Steering Committee (TSC) before the database lock. The plan will be uploaded to the ISRCTN website. Reporting of results will adhere to the relevant Consolidated Standards of Reporting Trials (CONSORT) guidelines. We define the target treatment effect as follows:

Population: 13- to 19-year-old adolescents from a randomised cluster (public mixed gender secondary school) who meet the trial inclusion/exclusion criteria and are identified as depressed by the PHQ-A (scoring 11 or more).Outcome: Depression scores at endline, 17 weeks post randomisation.Intervention: IPT compared to enhanced treatment as usual irrespective of treatment being discontinued (Intention to Treat, ITT).Population level summary measure: Individual mean PHQ-A score at 17 weeks post randomisation for each trial arm.Comparison: Mean difference between the trial arms at the participant-level at endline, 17 weeks post randomisation.

Following the principle of intention to treat (ITT) means adherence or compliance to allocated treatment is ignored and participants are followed up and analysed as part of their allocated groups. In this approach, data are collected after treatment discontinuation and missing data are included as if it was observed. The pattern of withdrawals in each trial arm will be assessed and any necessary remedial action will be approved by the TSC.

A descriptive summary of demographic and clinical variables at baseline and primary and secondary outcomes at baseline and post-randomisation (midline, endline and follow-up timepoints) will be reported by intervention group and overall. Mean, SD, medians and IQR will be used to summarise continuous variables and frequencies and percentages categorical variables respectively. Variables will be summarised at the cluster and individual level as appropriate.

The primary outcome of interest, the mean PHQ-A difference between the arms and 95% confidence intervals, will be estimated using mixed effects linear regression to take account of both the clustering due to the unit of randomisation being school and repeated measures by individual. The midline, endline and follow-up measures of the outcome measure are the dependent variable with a random intercept for cluster/school and an unstructured covariance matrix at the level of participant residuals to allow for repeated measures. This mmrm approach is preferred as it avoids model misspecification and is unbiased when data is missing at either random or completely at random [68]. The model will include the baseline measure of PHQ-A (ANCOVA approach), a dummy variable for trial arm, for timepoint and a trial arm by timepoint interaction to allow the treatment effect to vary across time. As randomisation is stratified by wave, this will always be included as a covariate in the analysis model. The model will be estimated using restricted maximum likelihood (REML) allowing the inclusion of all participants, with missing data as ignorable under the assumption of missing at random. Continuous secondary outcomes will be analysed using the same methods. Standardised effect sizes will be calculated by dividing the treatment arm difference estimate by the baseline standard deviation.

Model assumptions will be verified; linear mixed effects models assume residuals are normally distributed at the individual and cluster level and these will be checked appropriate data transformations will be applied if necessary and/or bootstrap procedures appropriate for multilevel models.

Model assumptions will be verified; linear mixed effects models assume that residuals are normally distributed at the individual and cluster level, which will be checked prior to analysis. Appropriate data transformations and/or bootstrap procedures appropriate for multilevel models will be applied if necessary.

To assess and report missing data, we will adhere to CONSORT guidelines. This includes presenting a table comparing baseline characteristics of patients with and without follow-up data, stratified by treatment arm, to identify potential bias. We do not expect any missing data at baseline, but if there is substantive missing data we will consider using multiple imputation by chained equations to address this. Missing data in the outcomes is accounted for by the designated mixed model estimated using restricted maximum likelihood estimation, which is valid under the ‘missing at random’ (MAR) assumption. This allows us to include all participants with at least one follow-up measurement to satisfy the ITT principle. To substantiate the MAR assumption, we will examine various baseline factors (e.g., demographics, clinical characteristics) as potential predictors of missingness and include significant predictors in the analysis model to improve its accuracy. As a sensitivity analysis, we will use multiple imputation with a substantive model which is consistent with the primary analysis model described above. Additionally, with multiple imputation we can consider using plausible ranges of patterns of missing data which allow departure from the MAR assumption based on the protocol of White et al., 2011 [69].

There are several planned additional secondary analyses of the primary outcome. To assess the effect of potential chance imbalance at baseline, effects of the size of grade 8- or 9-year groups per school will be controlled for and included as an additional covariate in the analysis models. Any changes in treatment effect will be noted. We will address the impact of treatment adherence using per protocol and Complier Average Causal Effects. In further secondary analysis we will evaluate CMOCs using planned multilevel mediation, moderation and moderated mediation analysis, noting that moderators (and potentially mediators) can occur at the cluster or individual level. These analyses are listed in Table 4.

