### Recruitment

We will approach schools initially by phone call and arrange to meet with the principal to explain the study and obtain approval. The team will then run an orientation session for teachers. Research assistants will visit classrooms to present the study to adolescents. All adolescents in the classrooms will be given a consent form and instructed to bring the consent form back (signed by themselves and a caregiver) if they are interested in being screened and potentially participating in the trial. Each signed consent form will be assigned an ID number. ID numbers will be randomly ordered using an online platform (e.g., https://www.random.org/lists/). The research assistants will invite adolescents for screening according to this random order and screen them for eligibility.

Based on our experience in the pilot cRCT, the optimum number of adolescents in an IPT group is eight, with a minimum of five. Based on depression prevalence estimates from our pilot cRCT, recruiting eight boys and eight girls from grades 8 and 9 would be feasible in large schools. However, in small schools we expect that even five might be challenging and in that case we may need to screen grade 7 students who fall within our target age range (13–19). Our experience suggests it is preferable to have smaller groups of adolescents from grades 8 and 9 than to have larger groups of adolescents from grades 7, 8 and 9. This is because facilitators in the pilot trial reported that groups combining students from grades 7, 8 and 9 tended to be less cohesive than groups with students from grades 8 and 9 only. Therefore, we will screen grade 7 only when it is necessary to form a group according to the following recruitment procedure:

In all schools we will initiate screening parallelly in grades 8 and 9 and continue until either:

(i)we recruit eight boys and eight girls (plausible in larger schools); or.(ii)we have screened all adolescents in grades 8 and 9.

If (ii) occurs and we have recruited fewer than five boys and/or five girls, we will initiate screening in grade 7 and continue until we have recruited eight boys and/or eight girls in total across the three grades, or until we have screened all adolescents in grade 7.

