### Assessment and follow up

We will conduct baseline surveys with adolescents before randomisation and collect data on demographic characteristics, primary and secondary outcomes and intermediate outcomes. We will also collect data on potential predictors and moderators of intervention effects including school climate, gender norms, adversity and socioeconomic status. We will measure school climate with an abbreviated version of the Beyond Blues School Climate Scale [55] and gender norms and adversity using select items from the Johns Hopkins Global Early Adolescent Study [56]. We will collect data on indicators of wealth including household assets and food security to generate a composite indicator of socioeconomic status. We will resurvey adolescents at midline, endline and follow-up, and for longer term follow up assessments at 12-, 18- and 30-months post randomisation. Based on the pilot cRCT, we expect a 92% response rate at endline.

We will also conduct surveys at baseline with adolescents’ parents (mother or father) to collect data on potential moderators of intervention effects. We will measure parents’ mental health using the General Health Questionnaire 12-item [57], parenting behaviour with the Alabama Parenting Behaviour Scale (involvement (10 items), positive parenting (6 items) and corporal punishment (3 items) subscales) [58] and disruptive behaviour with the Disruptive Behaviour International Scale – parent report [59]. We will survey parents again at endline to collect data for an economic analysis. If the adolescent does not have a parent or the parent is unavailable for interview, this will be recorded and linked to the adolescent’s data.

All surveys will be conducted by trained research assistants using tablets programmed with data collection software. Research assistants will read the survey questions to the participant and enter their responses on the tablet. We will conduct as many surveys as possible in person. Where we cannot meet the participant in person, we will conduct the interview on the phone. In-person surveys will be conducted in a private place at the participant’s school (adolescents) or home (adolescents and parents). For phone surveys, we will arrange a time for the survey in advance. Research assistants but not participants will be masked to allocation.

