The study also has limitations. First, implementing the trial in the Nepali education system is challenging. Schools often close at short notice due to staff strikes, heat and public holidays. These closures will impact the trial timeline, for example delaying randomisation, survey administration or IPT sessions, although schools in control and intervention arms are likely to be equally affected. Second, although cluster randomisation minimises contamination and is more acceptable and feasible than individual randomisation, it decreases the likelihood of balancing individual participant characteristics across trial arms. Third, in trials of psychological interventions, it is inherently impossible to mask participants to allocation. Intervention participants may show improved mental health outcomes because they know they are receiving IPT (known as the Hawthorne Effect), which could potentially lead to overestimation of intervention effects. To mitigate this effect, we will match the survey burden across trial arms to the extent that it is possible, conduct long term follow-up to explore whether effects persist beyond the trial period and use objective outcome measures where feasible including school attendance and examination grades. Fourth, trials of psychological interventions with treatment as usual or waitlist controls have been criticised because these control conditions do not match hours of therapist contact in the intervention arm and it is therefore impossible to test whether an intervention is effective because of its specific techniques or because of generic effects such as supportive human contact [70]. To address this criticism, we will implement an enhanced control condition with assessment and referral for high-risk cases and capacity building in local clinics. Moreover, our realist design will enable us to examine mechanisms through which IPT improves depression including specific techniques and general elements.

In conclusion, this realist cRCT of school-based group IPT has the potential to generate robust evidence for the effectiveness of psychological interventions in Nepal and will help to inform translation and optimisation of these interventions in other low-resource settings.

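### The sensitivity analysis for chance baseline imbalance adjusts only for year-group size, a school-level variable, while the imbalance the protocol warns of concerns individual participants

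*Protocol article*

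**What the plan says.** In the Quantitative analysis section, the primary model for PHQ-A is a mixed model for repeated measures with a random school intercept. On covariates it states: "The model will include the baseline measure of PHQ-A (ANCOVA approach), a dummy variable for trial arm", together with timepoint and the arm-by-timepoint interaction, and then: "As randomisation is stratified by wave, this will always be included as a covariate in the analysis model".

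Later in the same section the protocol lists secondary analyses of the primary outcome. The first opens with its purpose, "To assess the effect of potential chance imbalance at baseline", and names one covariate for it: "effects of the size of grade 8- or 9-year groups per school will be controlled for and included as an additional covariate". Any resulting change in the treatment effect is to be noted.

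The Discussion gives as the second limitation of the trial that, although cluster randomisation has practical advantages, "it decreases the likelihood of balancing individual participant characteristics across trial arms". It does not say which characteristics.

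The Assessment and follow up section says that the baseline survey, done before randomisation, will "collect data on demographic characteristics, primary and secondary outcomes and intermediate outcomes". Socioeconomic status is also collected then, and Table 2 lists GAD-7 and functional impairment at baseline.

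**The concern.** The stated purpose and the chosen covariate do not match. The purpose is to learn whether chance imbalance at baseline affects the result, and the protocol says that cluster allocation threatens balance between individuals. The single covariate named is a property of the school.

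Suppose the arms differed by chance in age, household poverty or comorbid anxiety. The sensitivity model as written would adjust for none of these directly. Its result could come back unchanged and be reported as reassurance on a question it had hardly tested. If the baseline table then showed an imbalance, there would be no covariate set named in this text to fall back on, and any further adjustment would look post hoc.

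**Working it through.** **1. Do other provisions already do this job?**
- Baseline PHQ-A is in the primary model and is the most important single covariate. It covers imbalance in baseline severity, but it need not capture age, socioeconomic status or comorbidity.
- Baseline factors can also enter through the missing-data clause: "we will examine various baseline factors (e.g., demographics, clinical characteristics) as potential predictors of missingness and include significant predictors in the analysis model". That selects on prediction of missingness rather than on prognosis, and only about 8% attrition is expected.
- Table 4 uses socioeconomic status (H11) and gender (H12) as moderators. Those analyses ask whether the effect or its mechanism differs between subgroups. They do not adjust the overall estimate.
- A baseline summary by arm will show an imbalance but does not assess its effect on the estimate.

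None of these is an analysis of chance imbalance in individual characteristics.

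**2. The protocol's own design effect.** Formula: DE = 1 + ((CV² + 1)m − 1) × ICC. With m = 12, CV = 0.16 and ICC = 0.07 this gives 1.79, as stated under Power and sample size. The formula is therefore safe to reuse.

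**3. How large can chance imbalance be at baseline?** Inputs from the protocol: 24 schools per arm, mean cluster size 13, CV 0.151. The covariate's ICC is not given, so the protocol's two PHQ-A values are borrowed.
- ICC 0.03: DE = 1 + ((0.151² + 1) × 13 − 1) × 0.03 = 1.37. SE of the standardised arm difference = sqrt(2 × 1.37/(24 × 13)) = 0.094. 95% range ±0.18 SD.
- ICC 0.07: DE = 1.86. SE = sqrt(2 × 1.86/312) = 0.109. 95% range ±0.21 SD.
- The chance of an imbalance beyond 0.2 SD is about 3% and 7% respectively.
- ICC 0.20 (assumed, for a strongly clustered covariate): DE = 3.46, SE 0.149, range ±0.29 SD, chance beyond 0.2 SD about 18%.

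These figures ignore stratification by wave. Waves group schools by area, so imbalance in geographically patterned covariates should be somewhat smaller than shown.

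**4. Shift in the treatment effect.** Shift = b × imbalance, where b is the association with endline PHQ-A left after baseline PHQ-A (assumed 0.1 to 0.3 SD per SD). At the edge of the 95% range:
- lower end: 0.1 × 0.184 = 0.018 SD; × 3.05 = 0.06 PHQ-A points;
- upper end: 0.3 × 0.214 = 0.064 SD; × 3.05 = 0.20 points;
- at ICC 0.20 and b = 0.3: 0.3 × 0.292 = 0.088 SD, or 0.27 points.

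For scale, the protocol puts its detectable difference at 0.9 points or less.

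**5. Precision.** Let R² be the share of remaining variance that the added covariates explain (assumed 0.03 to 0.10). With ICC 0.07 and 12 per school:
- individual-level variance only: SE ratio = sqrt([0.07 + 0.93(1 − R²)/12]/[0.07 + 0.93/12]) = 0.992 at R² = 0.03 and 0.973 at R² = 0.10;
- both levels: sqrt(1 − R²) = 0.985 and 0.949.

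The standard error therefore falls by about 1 to 5%.

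**6. Gender is a special case.** Recruitment aims at eight boys and eight girls per school, with five of each as the minimum group. As an illustration, let boys and girls per school each be uniform on 5 to 8 and independent (mean 6.5, variance 1.25). Per arm, the SD of the proportion of boys is about sqrt(2 × 24 × 1.25)/(4 × 24 × 6.5) = 7.75/624 = 0.0124. Between arms it is 0.0124 × sqrt(2) = 0.0176, and dividing by the SD of a balanced binary variable (0.5) gives 0.035 SD. That is about a third of the 0.109 SD in step 3.

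**The case against.** Four arguments on the other side carry weight.

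First, year-group size is not arbitrary. Grade 7 is screened only where grades 8 and 9 yield too few boys or girls, so the size of those grades bears on how many adolescents are recruited and on their grade and age mix. This stands, and it is the reason to keep the covariate. It remains an indirect, school-level proxy for part of one characteristic and does not reach poverty, anxiety or impairment.

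Second, the protocol defers to a detailed statistical analysis plan that is not shown. A missing covariate list would be no finding. The point here is narrower: the published text fixes both a purpose and a covariate, and the two do not fit. If the analysis plan names more covariates, the two texts need reconciling.

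Third, chance imbalance after randomisation is not bias. Its variability is already inside the standard error and the confidence interval. This stands in full.

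Fourth, baseline outcome plus the stratifier is a valid covariate set for the primary analysis. This also stands.

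A reader might go further and infer that the protocol identifies gender, age, socioeconomic status, anxiety and impairment as the factors at risk and then ignores them. The documents do not support that. The Discussion names no factors, several of these variables enter other models, and the list used here is only a reasonable example. A reader might also infer that gender should be in the primary model because recruitment and therapy groups are organised by gender. That does not follow either: a recruitment target is not a randomisation stratum, and step 6 of the working shows that the target largely balances gender across arms.

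**Conclusion.** The point holds as a mismatch between a stated purpose and the means chosen for it. The sensitivity analysis labelled for chance imbalance uses a school-level variable, while the risk that the protocol describes lies with individuals, so an unchanged estimate would be weak evidence on that risk. It is not an error in the primary analysis and does not threaten the validity of the main result.

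The size is modest: about 0.02 to 0.06 SD of shift per covariate at the edge of the 95% imbalance range, and a standard error gain of about 1 to 5%. These figures rest on assumed covariate ICCs (0.03 to 0.07), assumed residual associations (0.1 to 0.3 SD per SD) and an assumed additional R² of 3 to 10%, none of which the documents give. This is a cheap improvement, not a necessary correction.

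**What to change.** In the Quantitative analysis section, and in the statistical analysis plan when it is finalised, extend the chance-imbalance sensitivity model with individual prognostic covariates. Name them in advance and choose them for expected prognostic value, regardless of any imbalance later observed. Age, gender, socioeconomic status, baseline GAD-7 and baseline functional impairment would serve as an example set. Keep year-group size in the model, with a sentence tying it to the grade 7 recruitment rule. Leave the primary model with baseline PHQ-A and wave as it is.

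No new data are needed, because all of these are collected before randomisation. The cost is a few lines of wording, a few degrees of freedom and one slightly larger secondary model. The protocol has the analysis plan finalised before database lock and expects recruitment to run to November 2026, so there should be time to make the change.
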